## Methods: Data collection, management, and analysis

### Data collection methods

Before we include participants we will assess sociodemographic and profession-related data (medical specialization, years of professional experience) through the online survey for participating physicians. After a consultation with the SP, both the SP and the physician obtain a set of paper-based questionnaires (in T_0_ and T_1_). Consultations between the physician and the SP are recorded on video (by the SPs) and subsequently assessed by the research team. The evaluation of the intervention is conducted with an online survey after finishing either face-to-face (IG I) or online-training (IG II). In the case that participants fail to complete an online questionnaire, the project team sends a reminder via e-mail.

### Data management

Data management occurs in the study centers, and each center is responsible for its own data. Data entry will be conducted by study assistants. We aim to conduct reciprocal random checks on the quality of data entry. At the end of data collection, the data sets will be pooled for final analyses.

### Statistical methods

#### Statistical analyses

To test the main *hypothesis 1* an ANCOVA is conducted. The mean of the OPTION-12 at T_1_ serves as the dependent variable and the group factor (IG I, IG II, CG) serves as independent variable. The mean of the OPTION-12 at T_0_ serves as a covariate. Post-hoc tests using a Bonferroni correction will be conducted to analyze single contrasts. To test the secondary *hypotheses 2 and 3*, two ANCOVAS and post-hoc tests, comparable to the ANCOVA for *hypothesis 1*, will be conducted with the means of the SDM-Q-9 and QQPPI at T_1_ as dependent variable, the group as independent variable and the means of SDM-Q-9 and QQPPI at T_0_ as covariates. To test *hypothesis 4* regarding the satisfaction a *t* test for independent groups with IG I and II as independent variable and the mean of the 10 general items of the training evaluation as dependent variable will be conducted. For data management and analyzing, SPSS© will be used.

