#### Main hypothesis

##### Hypothesis 1

We hypothesize that in both intervention groups (IG I and II), physicians will show a higher level of external-rated SDM competence (assessed by OPTION-12 [36–38]; adjusted for T_0_) during their consultation with an SP 4 weeks after the training session (T_1_) compared to a CG (no training).

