### Sample size

The sample size calculation is based on the main *hypothesis1* and the method of analysis. A review of the efficacy of non-web-based SDM interventions [54] including five RCTs described significant comparisons in two of the five studies. In the significant studies, effect sizes were calculated as *d* = 1.06 and *d* = 2.11. Taking the non-significant results into account, a conservative estimation of effect size seems appropriate. Further, according to a meta-analysis [26], web-based trainings for physicians achieved high-range effect sizes regarding skills (Hedges’ *g* = 0.85) and behaviors/effects on patient care (Hedges’ *g* = 0.82). Therefore, an effect size of *d* = 0.50 is expected for the primary outcome (SDM competence assessed by OPTION-12 at T_1_ adjusted for SDM competence at T_0_).

The estimation of the sample size for a covariance-analysis (ANCOVA) is comparable to an analysis of variance (ANOVA) focusing on the difference between adjusted means. A power analysis via GPower Version 3.1.2 [55] for an ANOVA (one factor with three groups: IG I, IG II, CG) was performed. The results show with a type-1 error of 5% a sample size of 159 physicians is needed to detect a statistically significant effect size of *d* = 0.50 with a power of 80%. Due to randomization issues, a sample size of 162 participants is targeted.

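### Hypothesis 1 is two comparisons with the control group; Bonferroni-corrected post-hoc contrasts test them validly but with less power than a stepwise test at the same 5% family-wise error

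*Protocol article*

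**What the plan says.** The Main hypothesis section expects that "in both intervention groups (IG I and II), physicians will show a higher level of external-rated SDM competence" than the CG at T1, adjusted for T0. These are two directional comparisons, IG I with CG and IG II with CG.

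The Statistical analyses section tests this with an ANCOVA of OPTION-12 at T1 in which "the group factor (IG I, IG II, CG) serves as independent variable" and the T0 score is the covariate. It continues: "Post-hoc tests using a Bonferroni correction will be conducted to analyze single contrasts". Hypotheses 2 and 3 follow the same scheme with SDM-Q-9 and QQPPI.

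The Sample size section states that "an effect size of *d* = 0.50 is expected for the primary outcome", that the power analysis "for an ANOVA (one factor with three groups: IG I, IG II, CG) was performed", and that "The results show with a type-1 error of 5% a sample size of 159 physicians is needed" for 80% power. The target is 162, or 54 per arm.

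The article does not say how many contrasts the correction covers, whether the contrasts are run only after a significant F, or which contrast results would support Hypothesis 1.

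**The concern.** The three-group F test responds to any difference among the means, in any direction, including a difference between the two trainings. It is therefore not a test of Hypothesis 1, and the contrasts carry the primary question. They are labelled post hoc and given a correction stricter than the error target requires.

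What is at stake is power on the primary claim. The 80% in the sample size section belongs to the F test. The chance of showing that both trainings beat the CG is much lower, and the choice of correction lowers it further. Hypotheses 2 and 3 inherit the same rule.

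**Working it through.** **Inputs.** From the article: three equal arms of 54, type-1 error 5%, d = 0.50 on the T0-adjusted outcome. Assumed: two-sided tests (sidedness of the contrasts is not stated), a common residual SD of 1 on the adjusted scale, complete data, residual df = 162 − 3 − 1 = 158.

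**1. The plan's own figure.** Take f = d/2 = 0.25 (inferred; it reproduces the result) and λ = N·f². At N = 159, λ = 159 × 0.0625 = 9.94 and the three-group F test has 80.5% power. At N = 162, λ = 10.13 and power is 81.3%. The smallest N is 158, or 159 with equal arms. The stated 159 reproduces.

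**2. What the F test detects.** If both trainings lie 0.50 SD above the CG, the means are (0.5, 0.5, 0). Their variance is [2 × (1/6)² + (1/3)²]/3 = 1/18, so f = 0.236, λ = 162/18 = 9.0 and F power is 76.3%. If only one training works, the means are (0.5, 0, 0). The variance is the same, so the F test is again significant in 76% of trials, although Hypothesis 1 is then false. F cannot separate the two situations.

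**3. One contrast.** The noncentrality is 0.50 × √(54/2) = 2.598 on 158 df.
- Two-sided 5%: critical t 1.975, power 73.3%
- 5%/2: critical t 2.263, power 63.2%
- 5%/3: critical t 2.420, power 57.2%

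**4. Both contrasts.** The two contrasts share the CG, so joint power was simulated (1,000,000 trials per scenario). With both trainings at d = 0.50:

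| Rule | Each contrast | Both | At least one |
|---|---|---|---|
| Bonferroni over 3, after F | 57.0% | 41.1% | 73.1% |
| Bonferroni over 2, after F | 61.7% | 47.7% | 75.7% |
| Bonferroni over 2, no F gate | 63.2% | 47.7% | 78.7% |
| F at 5%, then each contrast at 5% | 67.7% | 59.2% | 76.3% |
| Holm on the two CG contrasts | 68.7% | 58.7% | 78.7% |
| Step-down Dunnett on the two CG contrasts | 69.3% | 58.9% | 79.7% |

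Dropping the F gate from Bonferroni over three changes nothing material (57% each, 41% both).

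**5. Error control.** With exactly three groups, any two pairwise equalities imply the third. Every intersection of pairwise nulls is therefore the global null, which F tests at 5%, so F followed by unadjusted 5% contrasts is a full closed test. Its simulated family-wise error is 5.0% under the global null and 5.0% when one pair is equal and the third group is far away. Bonferroni over three after F uses 4.2% and 1.7%. Holm and step-down Dunnett control the two CG contrasts at 5% by construction.

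**6. Other effects.**
- Effects 0.60/0.40: both contrasts 33.6% (Bonferroni over three), 39.8% (over two), 51% (Holm or closed).
- Effects 0.50/0.25: both contrasts 11.6% with Bonferroni over three, 22–23% with Holm or closed. For the stronger contrast the F-gated closed test gives 61.3%, ungated Bonferroni over two 63.0%, Holm about 64%.
- Only one training effective (0.50): that contrast has 57% with Bonferroni over three, 63% with ungated Bonferroni over two or with Holm, 68% with the F-gated closed test.
- 49 per arm (about 10% loss, an assumption), both at 0.50: both contrasts 35.7%, 42.3%, and 53–54% with Holm or closed.

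**The case against.** Bonferroni is a standard, valid correction and brings simultaneous intervals that agree with its tests. Preferring a stepwise method is a matter of efficiency. That stands: nothing here inflates error.

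The size of the gain depends on details the article leaves open. Against ungated Bonferroni over the two CG contrasts, the F-gated closed test gains only 67.7 − 63.2 = 4.5 points per contrast and loses 78.7 − 76.3 = 2.4 points for at least one. With effects 0.50/0.25 it is lower for the stronger contrast. That also stands, and it is why Holm or step-down Dunnett without an F gate is the better replacement. Holm rejects whenever Bonferroni over two or three CG-inclusive contrasts would reject a CG contrast, so it is never less powerful for these contrasts.

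A reader might infer that the plan would declare Hypothesis 1 proven on a significant F alone, and so claim both trainings when only one works. The article does not say so. It provides contrasts, and a one-training effect would show there. The missing element is a stated rule linking the contrasts to the word both. A reader might also infer that the contrasts are gated by F; that is a common reading of post hoc, but it is not written.

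The Discussion also aims to find out whether the two methods differ in efficacy. A third contrast, and a three-group F, are therefore defensible.

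Finally, if Hypothesis 1 is strictly a claim about both trainings, each contrast can be tested at 5% without correction, with 60.0% power. Holm gives up about one point against this and keeps family-wise control if only one training is claimed.

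**Conclusion.** The point holds as lost efficiency and as a mismatch between the hypothesis and its test. Bonferroni costs about 11 points (over two contrasts) to 18 points (over three) of power for the claim that both trainings work, and about 5 to 12 points per contrast, when both are at d = 0.50. For at least one contrast, Holm gains 5.6 points over F-gated Bonferroni over three and nothing over ungated Bonferroni over two; the F-gated closed test gains 3 points at most and can lose. If only one training works, Holm equals ungated Bonferroni over two.

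It would be wrong to conclude that a better correction rescues the power. Showing both contrasts remains at about 59% with 162 physicians, because the sample size was set for the F test.

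The figures assume two-sided tests, d = 0.50 on the adjusted scale unless stated otherwise, equal arms and complete data. The planned imputation of drop-outs was not modelled.

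**What to change.** Replace the post-hoc sentence with text to this effect: IG I–CG and IG II–CG are the planned contrasts of Hypothesis 1, estimated from the ANCOVA. They are tested by the Holm procedure (or step-down Dunnett) at a two-sided family-wise 5%, whether or not the overall group effect is significant. Hypothesis 1 is supported only if both contrasts are significant in favour of the intervention group. The same rule applies to Hypotheses 2 and 3.

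If all three pairwise contrasts are wanted as one family, because the trainings are also to be compared with each other, state instead that each is tested at 5% after a group effect significant at 5%. This shortcut is valid only for three groups, and it is more powerful than Bonferroni over three.

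The cost is a few lines of analysis text and no extra participants. The stepwise tests have no matching simultaneous intervals, so report adjusted mean differences with Dunnett or Bonferroni intervals separately and note that an interval may include zero where the stepwise test is significant. State also that the 80% power refers to the F test, and give the power for both contrasts beside it.

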#### Drop-outs and missing values

Participants, who drop out after T_0_, are considered for the main outcome (OPTION-12, no missing values at T_0_ due to inclusion/exclusion criteria II and nature of external rating) according to the intention-to-treat principle using a single imputation method, in more detail we impute the mean difference of other group (MOTH-D) [57]. Therefore, the mean difference (per item) between T_1_ and T_0_ of available cases in CG is added to T_0_ of drop-outs in IG I and II and vice versa the mean difference (per item) in IG I and II is added to T_0_ of drop-outs in CG. Additionally, an analysis with available cases which completed the study (analysis per protocol) will be reported in contrast.

Missing data in the ratings of the SPs (SDM-Q-9 and QQPPI; secondary outcome) due to drop-outs will be handled like the main outcome using MOTH-D. Additionally if missing data in a single item occurs in more than 50% of all questionnaires (T_0_ and T_1_) of available cases, this item will be deleted for all SP ratings because this item does not fit into the nature of consultations in this study. It is unlikely that missing values will emerge to a greater extent as SPs were reminded frequently to complete the questionnaire completely. However, single missing values in the SDM-Q-9 and QQPPI will be not imputed. Instead, a mean value is calculated with the remaining completed items of the questionnaire.

For analyzing the training evaluation missing cases will be imputed by the worst possible mean. An analysis with available cases will be conducted and compared.

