#### Secondary hypotheses

##### Hypothesis 2

In both intervention groups (IG I and II), physicians will show a higher level of SDM performance (assessed by SDM-Q-9 [39, 40]; adjusted for T_0_) rated by an SP during consultation 4 weeks after the training session (T_1_) compared to physicians in the CG (no training).

##### Hypothesis 3

In both intervention groups (IG I and II), physicians will show a higher level of quality in their physician-patient interaction (assessed by the Questionnaire on the Quality of Physician–Patient Interaction (QQPPI) [41]; adjusted for T_0_) rated by an SP during consultation 4 weeks after the training session (T_1_) compared to physicians in the CG (no training).

##### Hypothesis 4

Physicians receiving the individualized context-based SDM face-to-face training (IG I) will be more satisfied with the training (assessed by self-developed training evaluation) compared to physicians receiving the web-based interactive SDM online training (IG II).

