### Trial design

The study uses a bicentric, three-armed, randomized controlled, pre-post design. We will include 162 physicians who work either with colon cancer patients (stage II with risk factors) or breast cancer patients (stage II). In these two stages of disease patients are confronted with highly preference-sensitive decisions: For colon cancer stage II with risk factors (e.g., after an emergency surgery, perforation of the tumor, poorly differentiated tumor tissue) the German medical guidelines [42] recommend the use of SDM concerning the decision for or against chemotherapy after the surgical excision of the tumor. For stage II breast cancer the German medical guidelines [43] recommend SDM to choose between two possible options: breast-conserving surgery followed by obligatory postoperative radiotherapy or, alternatively, a complete removal of the breast. In each of the two IGs and in the CG, we aim to include 54 physicians. The study design and participant timeline are shown in detail in Fig. 1.

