### Implementation

The project team provides the result of the randomization to the participant by e-mail and coordinates the next steps in accordance to the result. For participants randomized to IG I, an appointment for the face-to-face-training is arranged, for participants of the IG II and CG an appointment for T_1_ is arranged and additionally for participants of IG II a link for the web-based interactive SDM online training is sent per e-mail.

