## Discussion

This trial will assess the effectiveness and acceptability of two innovative SDM training programs for physicians. We aim to analyze which improvements in SDM competence can be achieved by these training programs and their impact on the physician-patient interaction and to test if the dissemination methods differ regarding their efficacy.

Although we aim to meet the needs of the physicians in their daily routine, we anticipate some challenges in recruitment for the study. As the training is voluntary, it cannot be assumed that it can be performed during working hours. If the participants must complete the training in their leisure time, this could likely influence their motivation and, therefore, the expected effects of the training. Furthermore, face-to-face SDM training will be conducted by different members of the project team. Although we intend to standardize the coaching sessions, as far as possible, it cannot be avoided that there will be some differences between training lessons performed by different trainers. Although we train the SPs in oncological case vignettes to enable them to act in a standardized way, every SP brings his own personality and attitudes to the consultations. Furthermore, it is inevitable that the SPs will undergo an increase in medical knowledge as the study evolves and, therefore, may show a behavior change during later consultations. We will try to compensate for this by strictly monitoring consultations, and we will give additional training lessons if needed. We expect in IG I with face-to-face training to gain a higher level of satisfaction. However, for long-term implementation of the training, we assume that regarding the temporal expense an online tutorial is more feasible in daily routine compared to face-to-face coaching lessons. Despite these challenges, we also see several opportunities. Specifically, we consider our web-based training as an adequate and cost-effective way to convey SDM-related knowledge and competences. If this hypothesis is validated, then our training indicates that this training format should be extended to other medical areas. Furthermore, we consider our training to be an appropriate way to convey other communication-related challenges (e.g., breaking bad news) in daily medical practice.

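### Hypothesis 4: scoring missing training evaluations at the worst possible mean in both trained arms turns any difference in survey non-response into a satisfaction difference

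*Protocol article*

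**What the plan says.** All references are to the protocol article.

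- *Secondary hypotheses*, Hypothesis 4: physicians in IG I "will be more satisfied with the training (assessed by self-developed training evaluation) compared to physicians receiving the web-based interactive SDM online training". The *Discussion* repeats the direction: "We expect in IG I with face-to-face training to gain a higher level of satisfaction".
- *Statistical analyses*: a t test for independent groups compares IG I with IG II, with "the mean of the 10 general items of the training evaluation as dependent variable will be conducted".
- *Drop-outs and missing values*: "For analyzing the training evaluation missing cases will be imputed by the worst possible mean". The next sentence adds: "An analysis with available cases will be conducted and compared". The section does not say which of the two results settles Hypothesis 4 if they differ.
- *Interventions* and *Data collection methods*: the evaluation is an online survey in both trained arms, completed after the training, with an e-mail reminder to anyone who does not complete it.
- *Trial design*: "In each of the two IGs and in the CG, we aim to include 54 physicians".

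The article does not state the response range of the self-developed questionnaire, an expected mean or SD, or an expected response rate.

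**The concern.** Worst-value imputation is cautious when it penalises only the arm that is expected to win. Here both arms are trained and every non-responder in either arm gets the lowest score, so the arm with more non-responders looks less satisfied whatever its responders think. The article's rule for OPTION-12, SDM-Q-9 and QQPPI behaves differently: it gives drop-outs the mean change of the opposite group, which pulls the trained arms and the control group together. The satisfaction rule has no such property.

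If more evaluations are missing in IG II, the planned test can show the hypothesised IG I advantage when satisfaction is equal. If more are missing in IG I, it can show the opposite. If the arms lose equal shares, the block of lowest scores inflates the variance and can hide a real difference. Hypothesis 4 is the only one of the four stated hypotheses that sets the two training formats against each other.

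**Working it through.** **The plan's own figure.** The only calculation in the article is the total sample size for the primary outcome: "The results show with a type-1 error of 5% a sample size of 159 physicians is needed". It reproduces. For a one-way ANOVA with three groups and f = 0.50/2 = 0.25, the smallest N for 80% power is 158, or 159 as a multiple of three (power 0.805). It does not address Hypothesis 4, for which no power statement is given.

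**Inputs for Hypothesis 4.** From the article: 54 per arm and an independent-groups t test. Assumed, because the article does not give them: a 1-5 scale with worst value w = 1, responder mean 4.0, SD 0.6, a two-sided 5% test, and the non-response rates m1 (IG I) and m2 (IG II).

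**Expected difference.** With true means μ1 and μ2 and non-response unrelated to satisfaction within an arm, the imputed analysis estimates

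(1 − m1)μ1 − (1 − m2)μ2 + (m1 − m2)w.

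With equal true satisfaction μ this reduces to (m2 − m1)(μ − w), here (m2 − m1) × 3. It depends on the non-response gap and not on any difference in satisfaction.

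**Chance of a false IG I advantage.** This comes from simulation, with each physician's non-response drawn at random. Fixing the missing counts in advance would remove variation that the t test counts, and so distort the rates. The nominal rate in this direction is 2.5%.

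| Missing, IG I vs IG II | Expected spurious difference | Significant IG I advantage |
|---|---|---|
| 5% vs 10% | 0.05 × 3 = 0.15 | about 11% |
| 5% vs 15% | 0.10 × 3 = 0.30 | about 32% |
| 5% vs 20% | 0.15 × 3 = 0.45 | about 56% |
| 5% vs 25% | 0.20 × 3 = 0.60 | about 77% |

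Repeat runs differ by about one percentage point.

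**Hand check of 5% vs 20%.** The variance per arm is (1 − m) × 0.36 + m(1 − m) × 9.

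- IG I: 0.342 + 0.4275 = 0.77.
- IG II: 0.288 + 1.44 = 1.73.
- Standard error: √((0.77 + 1.73)/54) = 0.215.
- Expected t: 0.45/0.215 = 2.09, just above the critical value of 1.98, so a rejection rate slightly above one half is what one should see.

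**Sensitivity.**

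- Mean 3.5 with SD 0.8, and mean 4.5 with SD 0.5, give 42% and 62% for 5% vs 20%.
- In expectation, 0 vs 7 or 3 vs 11 missing evaluations out of 54 are enough for p < 0.05 (range 6 to 9, and 11 to 13).
- Reversing the gap to 20% vs 5% gives a false IG II advantage in about 55%.
- If IG II is truly better by 0.3 points, 5% vs 25% missing still gives a significant IG I advantage in about 29%.

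**Equal non-response.** At 10%/10% and 20%/20% the rejection rate under no difference stays at about 5%. At 10% the share of outcome variance due to imputed values is 0.81/(0.324 + 0.81) = 71%. Power for a true 0.3-point difference is then about 23%, against about 67% on available cases. The 23% is 27% if the true means are 4.0 and 3.7.

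**Available cases.** With equal true satisfaction and non-response unrelated to it, the two-sided rejection rate is 4.9% at 5% vs 20% missing and 5.1% at 5% vs 30%.

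**The case against.** The strongest reply is that the safeguard is already in the plan. The available-case result will be reported beside the imputed one, so a finding created by imputation would appear as a discrepancy, and the e-mail reminder should keep non-response low. This stands in part. It limits the harm, but the wording puts the imputed analysis first and does not say which result decides, and a reminder does not equalise response between arms.

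A reader might infer that the planned test measures non-response instead of satisfaction. The documents do not support that. With equal non-response the type I error holds, and the cost is attenuation and lost power.

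A reader might also infer that IG II will respond less and that the rule therefore favours the hypothesis. IG I has a personal coach, whereas "for participants of IG II a link for the web-based interactive SDM online training is sent per e-mail". But that sentence concerns access to the training, not the survey. The survey is online in both arms, and IG I has its own route to missing evaluations because a workplace appointment must first be arranged. The direction of any gap is unknown.

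Finally, available cases are biased too if dissatisfied physicians tend not to answer, which is plausible for a satisfaction survey. That stands, and is why the worst-value analysis should be kept, though not as the deciding one.

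**Conclusion.** The point holds as a fault in how Hypothesis 4 is analysed. Worst-mean imputation in both trained arms makes the comparison sensitive to differential non-response in either direction, and the plan has no rule for when its two analyses disagree. That the bias equals the non-response gap times the distance from the mean to the worst score follows from the rule itself, given equal true satisfaction and non-response unrelated to it. Every error rate and power figure rests on the assumed scale, mean, SD and non-response rates; with a small gap in response the distortion is modest. Hypothesis 4 is secondary. The primary outcome, Hypotheses 1 to 3 and the sample size are unaffected. The change should be made, but it does not threaten the trial's main conclusion.

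**What to change.** In *Drop-outs and missing values*, swap the roles of the two planned analyses:

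- State that the available-case t test decides Hypothesis 4. Multiple imputation by arm, using T0 and profession-related variables, is an alternative.
- Keep worst-value imputation as a sensitivity analysis.
- Add one scenario that works against the hypothesis: the worst value for IG I non-responders and the observed IG II mean for IG II non-responders.
- Report the survey response rate by arm.

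The swap costs about one sentence, and none of this needs new data or staff. The price is that the deciding test then relies on evaluations being missing at random, which the retained worst-value analysis and the added scenario are there to probe.
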